### Objectives and hypothesis

The first objective of this study was to investigate the effects of prone and lateral positions on patients receiving HFNO therapy in terms of ventilator-free days in 28 days and other prognostic factors. The secondary objective is to compare the differences in the impact of the prone and lateral positions on the investigated factors.

The hypothesis of this study is that positioning AHRF patients in the prone position can lead to improved prognoses. Additionally, for awake patients, the lateral position might be more beneficial than the prone position due to its better tolerance.

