### Experimental groups

The prone position group (Group A) will take the prone position on a horizontal bed for at least 1 h each time. Patients will be encouraged to take the position as many times as possible each day and remain in the prone position as long as possible each time if they are not tired. The investigators will insert a U-shaped pillow under each patient’s neck or chin and rectangular pillows under their shoulders, chest, hips, knees, and ankles. Then adjust the pillows to ensure their cervical and lumbar vertebrates are in functional positions and patients feel comfortable. Patients’ posture and pillow position can be adjusted at any time with anyone’s help. However, the patients must always keep the abdominal side down and parallel to the bed surface. (More details are provided in Additional file 4).

The lateral group (Group B) will be instructed to alternate lying on each side of their body at an 80°–90° angle on a horizontal bed for at least 1 h each time. Patients with a mono-lateral lung infection will be instructed to lie on the healthy side. Patients will put their upper arms and legs on quilts or pillows placed on the facing side. Their hips will be decompressed to prevent pressure injury. And they will be encouraged to lie on the same side for as long as possible each time and switch to the other side or take the supine position when they feel tired. One round is completed when the patients return to the semi-recumbent position for more than 10 min.

Patients in experimental Groups A and B will be told to change positions at least 1 h after a meal. We track the number of rounds and durations of each round for each assigned position on a daily basis. Only when the patient meets the standards of the corresponding position, and keeps it at least for 1 h at a time, will the duration be considered valid and recorded. Blood gas analysis will be performed daily and 1–2 h after returning to a semi-recumbent position on the first day.

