### Control group

Patients in the control group will take the semi-recumbent position (with the bed head elevated 30°–40°) which is the regular position taken by patients. Nurses will routinely instruct the patients to roll over and check vital signs every 2 h. Arterial blood gas will be measured daily. Patients in this group will not take the prone or lateral position unless their doctors think it is necessary.

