### Data collection and management

The outcomes will be measured during the intervention and 28 days after the patients are enrolled in the group. The data on the duration of different respiratory support, hospital and ICU lengths of stay, and hospitalisation cost will be collected at discharge or the 28th day after enrolment, whichever occurs first. (The data collection schedule is shown in Table 1). Trained nurses will assess the Borg scale score and fill in the bedside inspection forms (Additional file 6) with average vital signs within 3 min at each allotted timepoint and position change time of each round. Supervisors will examine and transcribe inspection forms every day. Two trained researchers who do not know patients’ allocations will check and collect all other data extracted from the electronic medical record system, including data on withdrawn patients. The main researchers will explain every detail of the parts each researcher is responsible for through online or physical training with a set of standard teaching materials, check the training effect through a test, and give one-to-one guidance to every researcher according to their results.

**Table 1 Tab1:** Data collection schedule

Study Period	Timepoint	Assessments
Enrolment	Day 0–1	Eligibility
		Informed consent
Allocation		Baseline information
		PaO_2_/FiO_2_ ratio after receiving HFNO therapy for 2 h
Post-allocation	During interventions (Day 1–termination)	Vital signs
		PaO_2_/FiO_2_ ratio
		Borg scale
		Position changing time (experimental groups only)
		ROX index
		Special treatments
		Respiratory support
		Adverse events
	At discharge/Day 28	Hospitalisation cost
		Number of hours using HFNO
		Number of hours using advanced respiratory support mode
		Number of hours using conventional oxygen therapy
		Length of hospital and ICU stay
Close-out	At Day 28	Death
		Endotracheal intubation

The confidentiality of the data will be preserved when the coded, anonymised data are transmitted and stored at the location of the statistician in charge of the final analysis.

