### Statistical methods for the primary and secondary outcomes

Analysis of variance will be used for ventilator-free days in 28 days, the number of hours using HFNO, noninvasive ventilation, invasive mechanical ventilation, length of hospitalisation, and hospitalisation cost. When it indicates that at least one group is significant, the Bonferroni correction will be applied.

For the 28-day mortality rate and 28-day intubation rate, we will conduct a survival analysis with the Kaplan-Meier method. We will compare the mortality and intubation rates of the three study groups using a log-rank test. We will use the Cox proportional hazards model to detect the relationship between diagnosis, onset time, PaO_2_/FiO_2_ ratio change, the duration of changing positions, and total position changing time.

Other secondary outcomes, such as the change in the PaO_2_/FiO_2_ ratio, ROX index, Borg scale score within the groups, will be compared with a paired repeated measures analysis of variance or generalised estimating equation based on the integrity of the data. The incidence of adverse events will be analysed using either the chi-square test or Fisher’s exact test. Univariate and multivariate analyses of risk factors for prone position failure will be performed with logistic regression.

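### The Cox model for intubation and mortality omits the randomised arm, so no arm hazard ratio is planned and its position-time terms are confounded with arm

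*Protocol article*

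**What the plan says.** All references are to the protocol article.

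- *Statistical methods for the primary and secondary outcomes*: 28-day mortality and intubation are analysed by Kaplan-Meier, and "We will compare the mortality and intubation rates of the three study groups using a log-rank test". The next sentence gives the Cox model: "We will use the Cox proportional hazards model to detect the relationship between diagnosis, onset time". Its list goes on to PaO2/FiO2 change and closes with "the duration of changing positions, and total position changing time". Randomised arm does not appear, and nothing marks the list as examples only.
- *Data collection and management*, Table 1: "Position changing time (experimental groups only".
- *Experimental groups*: a spell counts only when the patient holds the proper position and "keeps it at least for 1 h at a time, will the duration be considered valid and recorded".
- *Control group*: "Patients in this group will not take the prone or lateral position unless their doctors think it is necessary". The schedule collects no hours for such patients.
- *Objectives and hypothesis*: one objective is "to compare the differences in the impact of the prone and lateral positions on the investigated factors", and the hypothesis is that "the lateral position might be more beneficial than the prone position due to its better tolerance".
- *Methods for additional analyses*: Bonferroni correction for pairwise comparisons among the three groups.

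**The concern.** There are two consequences.

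First, the objectives call for three contrasts: prone against control, lateral against control, and lateral against prone. A log-rank test yields a p-value, and corrected pairwise tests yield more p-values. The Cox model would normally supply the hazard ratio and its interval, but without an arm term it cannot.

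Second, position time is tied to arm by design. It is recorded only in Groups A and B, and the trial's own hypothesis expects better tolerance, hence more hours, in the lateral group. A model with hours but no arm cannot tell longer positioning from a different position. The *Background* and *Discussion* treat the time-effect relationship as an open question, and the *Discussion* infers a benefit from at least 8 hours a day. An hours coefficient is therefore likely to be read as dose-response.

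This is distinct from the fact that position time accrues after randomisation. Handling it as time-dependent would not put arm into the model.

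**Working it through.** The article states no figure for the Cox analysis, so there is none to reproduce. The check has four steps.

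**1. Inputs**

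- Patients per arm: 583 / 3 ≈ 194 (*Sample size*, *Trial design*).
- Event rates: 43% (intubation) and 19% (28-day mortality), from *Background and rationale*. These are background figures for HFNO patients. The 43% carries no 28-day label there, and neither is a control-arm assumption of this trial. They are used as illustrations.
- Assumed, not in the article: arm hazard ratios as given below; mean 5 hours a day prone and 8 lateral, SD 2, fixed from the start; no effect of hours within an arm.
- Event times: exponential, censored at day 28, control hazard −ln(1 − rate)/28 per day. That is 0.0201 at 43% and 0.0075 at 19%.

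**2. What an arm hazard ratio would offer**

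For one pair of arms the 95% interval is the estimate multiplied and divided by exp(1.96 × 2/√events).

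- Intubation: events = 2 × 194 × 0.43 ≈ 167; exp(3.92/√167) = 1.35.
- Mortality: events = 2 × 194 × 0.19 ≈ 74; exp(3.92/√74) = 1.58.

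These are informative intervals, and the plan as written does not ask for them.

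**3. Controls entered as zero hours**

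True hazard ratio 0.7 in both positions. Share of simulated trials in which hours reach p < 0.05:

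| Event rate | Without arm | With arm |
|---|---|---|
| 43% | about 55% (hazard ratio per hour 0.96) | about 4-6% |
| 19% | about 25-32% | about nominal |

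The Monte Carlo standard error for 55% with 400 trials is √(0.55 × 0.45/400) ≈ 2.5 points.

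Sensitivity to the spread of hours: with gamma-distributed hours (shape 4, so SD is half the mean: 2.5 and 4), the shares without arm are 46% at a 43% event rate and 19% at a 19% event rate. Hours then stand in for arm less closely. With that same spread, a hazard ratio of 0.6 in both arms gives 68% and 39%. When the arms do not differ at all, the share is 5.5%, so it is the arm effect that leaks into the hours term.

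**4. Controls dropped, Groups A and B pooled without arm**

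- Equal effects in A and B: about 4-6%, which is nominal.
- Hazard ratios 0.7 prone and 0.9 lateral: about 11-16% at a 43% event rate and about 8% at 19%. With arm in the model, or stratified by arm, it is about 5-6%.
- Hazard ratios 0.6 and 0.8 with the wider spread of hours: 10%, with a hazard ratio per hour of 1.016. More hours look slightly harmful only because the better tolerated position is assumed to be the weaker one. With arm: 5%.

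Dropping controls also removes about 194 of 583 patients. Coding them as zero may be wrong for any control patient whose doctor orders a position change.

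**The case against.** The strongest reply is that the arm comparison is not missing. Kaplan-Meier curves give each arm's 28-day risk and so the direction and absolute difference, the log-rank test is a valid randomised comparison, and pairwise correction is provided for. The Cox sentence can be read as a separate prognostic or duration analysis, and an article may leave full model specification to an analysis plan. Since hours exist only in Groups A and B, a model confined to those groups, perhaps fitted by arm, is a more natural reading than zero-coding. The trial is labelled exploratory and these are secondary outcomes.

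Much of this stands. A reader might infer that the plan gives no size or direction of effect for intubation and mortality. The Kaplan-Meier analysis rules that out. A reader might take this Cox model for the only regression planned. The same section also plans logistic regression and possibly generalised estimating equations. Nor does the article say that controls are coded as zero or that A and B are pooled.

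What does not stand is that this is merely unstated detail. The article fixes a list of Cox terms, and arm is not on it. Even as a prognostic model, its position-time terms are confounded with arm unless it is fitted within arm or stratified by arm, and the text says neither.

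**Conclusion.** The point holds in limited form. As written, no hazard ratio with an interval is stated for any of the three contrasts on intubation or mortality, and the position-time term is confounded with arm.

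The size depends on how controls enter, which the article leaves open. With zero-coding the confounding is strong: about 55% false significance at an assumed 43% event rate and about 25-32% at 19%. With controls dropped it is modest: nominal under equal effects, about 8-16% at hazard ratios of 0.7 and 0.9. The 55% should not be read as the error rate to expect in this trial, because it belongs to one coding and one assumed scenario. All the hours and hazard ratios are assumptions.

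This is a secondary analysis, and the analysis of variance on ventilator-free days is untouched. The change is still worth making, because the better model costs only wording.

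**What to change.** In *Statistical methods for the primary and secondary outcomes*:

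1. For 28-day intubation and mortality, specify a Cox model with randomised arm as a factor, stratified by centre and PaO2/FiO2 layer. Include no post-randomisation covariates, so neither position time nor PaO2/FiO2 change. Report hazard ratios with 95% confidence intervals for prone against control, lateral against control and lateral against prone, beside the log-rank test.
2. Move position time to a separate model labelled exploratory, in Groups A and B only, with arm and an arm-by-hours term. Handle position time as time-dependent or by a landmark, since adding arm does not cure the fact that hours accrue only while the patient remains at risk.

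No new data, visits or patients are needed. The cost is slightly less precision for the hours term, because arm shares information with it.

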#### Secondary outcomes

28-day intubation rate (intubation is defined as endotracheal intubation and receiving invasive mechanical ventilation);28-day all-cause mortality(defined as death caused by all kinds of diseases within 28 days after randomisation);Change in the daily PaO_2_/FiO_2_ ratio (measured every morning around the same time) during intervention;Change in daily Borg scale score;Daily and total position changing time;Change in daily ROX index: SpO_2_/FiO_2_ to respiratory rate;Number of hours receiving HFNO therapy;Number of hours receiving noninvasive mechanical ventilation and invasive mechanical ventilation;Treatment failure rate (defined as patients who receive noninvasive, invasive ventilation or die after taking assigned positions);The incidence of adverse events;Length of hospital stay and ICU stay.Hospitalisation cost.

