### Methods for additional analyses

We will conduct subgroup analyses based on the PaO_2_/FiO_2_ ratio (PaO_2_/FiO_2_ > 200 mmHg or ≤ 200 mmHg), time from admission to intervention implementation (< 24 h or ≥ 24 h), position changing time, and different diagnoses. The Bonferroni correction will be used for pairwise comparisons among the three groups. We will handle the missing values of withdrawn patients with the intention-to-treat the analysis and use multiple imputation. We will also do a per-protocol analysis if patients in the supine position group take the intervention that the experimental groups have. Since this is a multicentre study, centre-effect analysis will be implemented.

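### Total position time, cut short by both failure and recovery, is planned as a Cox covariate and a subgroup factor: the association can be spurious in either direction, and the subgroup has no control comparator

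*Protocol article*

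**What the plan says.** All places are in the protocol article.

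- **Statistical methods for the primary and secondary outcomes.** "For the 28-day mortality rate and 28-day intubation rate, we will conduct a survival analysis with the Kaplan-Meier method", with log-rank comparison of the three arms. Then: "We will use the Cox proportional hazards model to detect the relationship between diagnosis, onset time", followed by PaO2/FiO2 change, "the duration of changing positions, and total position changing time". The sentence names no dependent variable; its place implies intubation and death. It does not say whether the terms are fixed or time-dependent.
- **Indications for terminating the intervention.** Positioning stops on deterioration (noninvasive ventilation, intubation, death). It also stops on improvement: low flow with PaO2/FiO2 above 300 mmHg for 6 h, or adequate saturation on conventional oxygen.
- **Methods for additional analyses.** Besides baseline PaO2/FiO2, the subgroup factors are "time from admission to intervention implementation (< 24 h or ≥ 24 h), position changing time, and different diagnoses". Bonferroni-corrected pairwise comparisons of the three groups are planned next.
- **Data collection and management, Table 1.** The entry for the position variable reads "Position changing time (experimental groups only", closing bracket omitted here.
- **Secondary outcomes.** Treatment failure is "defined as patients who receive noninvasive, invasive ventilation or die after taking assigned positions", whereas ventilator-free days and mortality run from randomisation.

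**The concern.** A patient intubated on day 2 cannot accumulate more than two days of positioning. A patient who stays on HFNO for ten days can. If each patient's total is related to intubation or death, part of what is estimated is time on HFNO, and that time is determined by the outcome itself. PaO2/FiO2 change during the intervention has the same structure.

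The subgroup problem is simpler. Controls have no recorded position time, so they cannot be placed in any level. Comparing prone with lateral inside a level is not clean either, because it conditions on tolerance, which the protocol's own hypothesis expects to differ between those arms.

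At stake is how a dose-response result would be read. The Discussion already infers that a median of at least 8 h of prone positioning a day helps prognosis, and a spurious hazard ratio could be taken as confirming or contradicting that.

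**Working it through.** **The plan's figures.** The protocol gives none for the Cox or subgroup analyses. The sample size supplies the number of patients. With means 19, 23 and 22 the squared deviations from 21.33 sum to 5.44 + 2.78 + 0.44 = 8.67. At a common SD of 12 (the mean of 13, 12 and 11) and 162 per arm, the noncentrality is 162 × 8.67/144 = 9.75 and the power is 0.802. So 3 × 162 = 486 reproduces, and the two position arms hold 2 × 162 = 324.

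**Mechanism.** Let h be a patient's hours per day and T the days until positioning ends, so T = min(failure time, recovery time). The total is H = h × T, and the model is hazard(t) = hazard0(t) × exp(β·H/10). At an event time t the failing patient has T = t and is compared with those still at risk.

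- If recovered patients are followed to day 28, the risk set mixes patients with T above t and recovered patients with T below t. The sign depends on the mix.
- If recovered patients are censored when HFNO stops, everyone else at risk has T at or above t. The hazard ratio is then pushed below 1.

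For illustration, at 5 h/day, failure at 3 days and recovery at 6 give 15 h against 30 h. Reversing the timings reverses the contrast.

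**Simulation with no effect of position.** There were 300 trials of 324 patients. Failure was set at 43%, the intubation rate in the Background. Assumptions: exponential times on HFNO with the means below, and about 5 h/day independent of outcome. Entries are the hazard ratio and the share of trials with p<0.05. The ratio is per 10 h, except per 1 h for mean daily hours.

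| Mean days to failure / recovery | Total, followed to day 28 | Total, censored at end of HFNO | Mean hours per day | Day-2 landmark, still on HFNO |
|---|---|---|---|---|
| 3 / 6 | 0.76 (100%) | 0.42 (100%) | 1.00 (3%) | 1.01 (5%) |
| 4 / 5 | 0.90 (76%) | 0.54 (100%) | 1.00 (6%) | 0.995 (5%) |
| 5 / 5 | 0.96 (24%) | 0.61 (100%) | 1.00 (4%) | 0.995 (8%) |
| 5 / 4 | 0.995 (2%) | 0.61 (100%) | 1.00 (3%) | 1.01 (4%) |
| 6 / 3 | 1.06 (84%) | 0.68 (100%) | 1.00 (5%) | 1.01 (5%) |

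For 28-day death (19%, also from the Background), the fixed total gave 0.82 (80%) at 3/6, 0.99 (3%) at 5/5 and 1.07 (57%) at 6/3.

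**Sensitivity to the recovery distribution.** A second null model used intubation at 0.08 per day and mean recovery at 8 days. The fixed total gave 0.83 per 10 h (97%) with gamma(2,4) recovery times but 0.97 (17%) with exponential ones.

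**Does the remedy need care?** In that second model, time-updated hours with recovered patients left in the risk set gave about 1.33 (98%), a false harm. A day-2 landmark among all event-free patients gave 1.21 to 1.63 (19% to 80%). Recovered patients stop accruing hours and no longer fail. Restricting to patients still on HFNO gave about 1.0 (about 3% to 10%).

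**The case against.** Four points on the other side carry weight.

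1. **The protocol never calls the covariates fixed.** That is an inference, natural for a quantity called a total. The separately listed duration of changing positions may mean time per day, and mean daily hours showed no artefact here. This stands for the daily term, although the simulation assumed daily hours unrelated to prognosis. It does not rescue the total. A separate analysis plan may settle the handling, but the choice of a total as covariate, and of position time as a subgroup, is made in this document.
2. **A reader might infer a certain false benefit of longer positioning, of the immortal-time kind.** The documents do not support that. Positioning also ends at recovery, which pulls the other way; with follow-up to day 28 the bias can be nil or reversed. Only censoring at the end of HFNO gave a ratio below 1 throughout, and the protocol does not specify that censoring.
3. **A reader might treat time to implementation as another such covariate.** It is not in the Cox list; an undefined onset time is, and the two cannot be equated. The clock for "time from admission to intervention implementation" starts at admission, and under Recruitment positioning begins as soon as possible after allocation, so most of it has elapsed before randomisation. Its weakness is narrower: implementation has no clear meaning for controls or for patients who never start.
4. **These are secondary analyses in a trial labelled exploratory.** The dose-time relationship is background and discussion material; it is not among the listed objectives. This limits the consequence but not the fault.

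On treatment failure, the assigned positions include the semi-recumbent one and positioning starts promptly, so few failures may precede a first session. The documents give no number. The start point still differs from that of the other outcomes.

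**Conclusion.** The point holds in a limited form. Total position time and PaO2/FiO2 change arise after randomisation and are cut short by the events being modelled and by recovery. As a single value per patient, total time can show an association where none exists. Under the assumed timings the null hazard ratio per 10 h was 0.76 to 1.06 with follow-up to day 28, with false-positive rates from 2% to 100%. These figures rest on assumed failure, recovery and daily-hours distributions, for which the protocol gives no data, so they show that the sign and size are uncontrolled and do not forecast a result. PaO2/FiO2 change was not simulated; the argument there is structural.

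The subgroup finding needs no simulation: with no position time recorded in controls, a split by "position changing time, and different diagnoses" offers no randomised comparison with control on its first factor. The 24 h subgroup and the treatment-failure start point are smaller matters of definition. The primary ANOVA and the log-rank comparisons are not affected.

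**What to change.** - Remove position changing time from the subgroup list.
- Run exposure-response in the two position arms only. Use hours accrued up to a landmark (for example days 1–2) or time-updated hours, in either case restricted to patients still on HFNO and event-free. Treat PaO2/FiO2 change the same way. State the dependent variable and label the result non-randomised. For mortality the landmark is the more practical choice, since follow-up confined to time on HFNO would lose deaths after intubation.
- Define the 24 h subgroup by time from admission to randomisation, which exists for every patient in every arm.
- Count treatment failure from randomisation in all arms, as ventilator-free days and mortality already are.

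The cost is wording: rounds and their durations are already recorded daily. The landmark drops early events and early recoveries from that one exploratory analysis and so loses some precision there. Restricting to patients still on HFNO is essential; without it the remedy introduces its own bias.

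### Change in PaO2/FiO2, ROX index and Borg score is set to be analysed within each arm, with no between-arm contrast stated for these three secondary outcomes

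*Protocol article*

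**What the plan says.** The Secondary outcomes section of the protocol article lists three longitudinal measures: "Change in the daily PaO_2_/FiO_2_ ratio (measured every morning around the same time) during intervention", "Change in daily Borg scale score" and "Change in daily ROX index: SpO_2_/FiO_2_ to respiratory rate".

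Their analysis is given once, in the section Statistical methods for the primary and secondary outcomes. One sentence covers all three measures and ends its list with this rule: "Borg scale score within the groups, will be compared with a paired repeated measures analysis of variance". It then offers a second method as an alternative: "or generalised estimating equation based on the integrity of the data". The sentence states no arm effect, no arm-by-time term and no comparison with control.

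For mortality and intubation, the same section does state a between-arm test: "We will compare the mortality and intubation rates of the three study groups using a log-rank test". Ventilator-free days and the other duration and cost outcomes get an analysis of variance across groups, followed by Bonferroni correction.

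Under Objectives and hypothesis, the second objective is to "compare the differences in the impact of the prone and lateral positions on the investigated factors". The Discussion describes the trial as comparing both positions with the semi-recumbent position.

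**The concern.** Two terms in the sentence, *within the groups* and *paired*, point the same way: each arm is compared with its own earlier values. The objectives need contrasts between arms. A change inside one arm mixes any effect of position with everything else that happens over time. Under Interventions, flow and FiO2 are adjusted dynamically in all patients, and the illness itself evolves. Only the contrast with a concurrent randomised arm removes these influences.

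If the sentence were followed literally, the oxygenation and dyspnoea outcomes would be reported without using the randomisation. A significant change in a position arm would say nothing about position versus control, and nothing about prone versus lateral.

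**Working it through.** **1. The text side by side.** Within one section, mortality and intubation are compared across the three groups by a log-rank test, and the duration and cost outcomes by analysis of variance across groups. Only the three longitudinal outcomes are described as change within the groups and as paired. The difference in wording falls on exactly the outcomes for which no between-arm contrast appears.

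**2. The plan's own figure.** The protocol gives no design figure for PaO2/FiO2, ROX or Borg. Its only sample size is for ventilator-free days: means 19, 23 and 22; SDs 13, 12 and 11; two-sided alpha 0.05; power 0.8; 486 evaluable patients at 1:1:1 (Sample size section).

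- Overall mean = (19 + 23 + 22)/3 = 21.33. Sum of squared deviations = 5.44 + 2.78 + 0.44 = 8.67.
- Common variance = (169 + 144 + 121)/3 = 144.67, so SD = 12.03.
- Noncentrality = 162 × 8.67/144.67 = 9.7. Power from the noncentral F distribution with 2 and 483 degrees of freedom = 0.800.

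The figure of 486 is reproduced and gives 486/3 = 162 per arm, used below.

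**3. Illustration of what within-arm tests can show.** Assumptions, none from the documents: the same true change of d SDs (SD of the change) in all three arms, so no effect of position; independent arms; a paired test in each arm at two-sided 0.05, normal approximation. The paired test is a simple stand-in for a within-arm repeated-measures test.

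- Probability that one arm is significant: p = Φ(d√162 − 1.96) + Φ(−d√162 − 1.96), with √162 = 12.73.
- Probability that at least one position arm is significant: 1 − (1 − p)².
- Probability that at least one position arm is significant while control is not: (1 − p)[1 − (1 − p)²].

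| d | p | At least one position arm significant | Position arm significant, control not |
|---|---|---|---|
| 0.1 | 0.247 | 0.432 | 0.326 |
| 0.2 | 0.721 | 0.922 | 0.257 |
| 0.3 | 0.968 | 0.999 | 0.032 |
| 0.5 | 1.000 | 1.000 | 0.000 |

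Worked case, d = 0.2: 0.2 × 12.73 = 2.55; 2.55 − 1.96 = 0.59; p = 0.721. Then 1 − 0.279² = 0.922, and 0.279 × 0.922 = 0.257.

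The true between-arm difference is zero in every row, yet the pattern of significance ranges from frequent disagreement between position and control to near-certain significance everywhere. The pattern follows the size of the common change, not any effect of position.

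**The case against.** The strongest reply is that the sentence can be read more kindly. *Within the groups* may describe the change that is then compared between arms, and *paired* may only mean repeated measurements on one patient. Both repeated-measures analysis of variance and GEE can carry arm and arm-by-time terms. The objectives and the Discussion make comparison between positions the purpose of the trial. The section Methods for additional analyses adds: "The Bonferroni correction will be used for pairwise comparisons among the three groups". The article is also a condensed account, and covariates and model terms are usually settled elsewhere.

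Part of this stands. GEE is named as an alternative, so the plan is not confined to paired tests, and the looser reading is possible. The exact model terms would not be a finding on their own. But the looser reading fits poorly with the two terms used together, and a method that could carry an arm term is not a stated arm contrast. The Bonferroni sentence follows the list of subgroups and names neither an outcome nor a model. The point is also not one of missing detail: the article does state a comparison, and it is the wrong one for the objectives.

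Three stronger readings are tempting and are not supported:

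- **That every arm, control included, will improve significantly.** No expected change is given for these outcomes. The Background cites an HFNO failure rate of up to 48%, and the intervention ends on improvement or on deterioration, so even the direction of the average change is unknown.
- **That the arms will be judged by whose within-arm p-value is significant.** The protocol nowhere says so; the table shows only what such an inference would be worth.
- **That all arms will be significant and that they will often disagree.** These belong to different rows of the table and cannot both hold for one outcome.

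**Conclusion.** The concern holds in limited form. As written, the analysis of change in PaO2/FiO2, ROX index and Borg score is a within-arm comparison, by repeated-measures analysis of variance or GEE, with no between-arm contrast stated. It therefore does not address the comparisons that the objectives call for.

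The size cannot be derived from the protocol. Under the assumptions above, with no effect of position, the chance that a position arm is significant while control is not is about 0.33, 0.26 and 0.03 at a common change of 0.1, 0.2 and 0.3 SD. It is practically nil at 0.5 SD, where all arms are significant.

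The scope is three secondary outcomes of a trial that calls itself exploratory. Ventilator-free days, mortality and intubation have tests across the three groups and are untouched. This should be corrected, but it does not threaten the main result.

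**What to change.** Reword the sentence. Remove *within the groups* and *paired*, and state that the three outcomes will be compared between arms with the repeated-measures model or GEE already named. The model should contain arm, day and arm-by-day, adjusted for the baseline value and the randomisation strata (centre and PaO2/FiO2 layer). Report the prone–control, lateral–control and prone–lateral differences with confidence intervals. Present within-arm change as descriptive only.

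The cost is a change of wording. Table 1 already schedules all three measures during the intervention, and PaO2/FiO2 at allocation. It does not itemise its baseline information, so the sponsor should confirm that a pre-intervention Borg score and ROX index are part of it.
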